### Primary outcome

For LVMI, we will undertake univariate (single outcome) endpoint analysis. Score residuals will be checked for approximate normality and an appropriate normalising transformation applied to the endpoint data if appropriate and possible. We will use analysis of covariance (ANCOVA) to estimate the treatment effect, adjusting for baseline and potentially adjusting for covariates, if applicable. The resulting treatment contrast will be reported as a point estimate and as a 95% confidence interval.

### Secondary outcomes

For all secondary outcomes other than health-related quality of life, we will undertake multivariate (repeated outcomes) endpoint analysis. For health-related quality of life, we will use univariate analyses in a manner similar to that presented for the primary outcome. Otherwise, analyses will fit all outcomes as repeated measures over the 2–4 assessment time points to an appropriate regression model using generalised estimating equations (GEEs). Changes from baseline will be associated with the assessment time (from baseline), the treatment arm, and the interaction of the two, adjusting for baseline and potentially for other confounding covariates, if applicable, similarly to the procedure outlined above for the primary outcome. The procedure will account for clustering on subjects; independent, exchangeable and autoregressive working correlation structures will be used and the best option in terms of Quasilikelihood Information Criterion retained for the final analyses [176]. Time-averaged analyses will be implemented by appropriately weighting each observation, accounting for any missing time point, so as to produce inference on the estimated average value over the available individual follow-up period. All results will be estimates of treatment effect and treatment-time interaction contrasts. Results will be reported as the point estimates and 95% confidence intervals for these quantities.

### Contingency for non-normality

Equivalent analyses after a normalising data transformation will be carried out if non-normality of outcomes is evinced. The choice of transformation will be guided by the stabilisation of variance. Notable departures from normality of residuals after regression of the transformed data, as evinced by visual assessments and formal tests of normality of residuals, will result in an alternative approach. When a transformation is applied, location estimates and confidence intervals will be transformed back to the original scale, with first-degree bias correction.

### Missing data

Every effort will be made to minimise missing data. Missing outcome data will cause the patient/time point instance to be removed from the analysis. In the case of time-averaged endpoints, non-missing data will be appropriately reweighted. Joint modelling of missingness and the primary outcome will be carried out, for sensitivity assessment, if missingness exceeds 10% or is significantly different between the intervention arms at the 5% level.

### Subgroup analyses

Subgroup analyses will be performed for the primary outcome and time-averaged BP (intra-dialytic, inter-dialytic, percentage maximum recommended daily dose of antihypertensives) according to the baseline severity of LV hypertrophy, baseline severity of hypertension, and baseline pre-dialysis plasma γNa. Subgroup analyses will be carried on using interaction of the groups thus defined and the treatment arms.

### Tolerability analysis

Tolerability of dialysis will be compared between the two arms by assessing the frequency of intra-dialytic hypotension episodes using negative binomial regression of the number of events as dependent variable and the logarithm of the duration of the period covered (normally two weeks, prior to assessment). To identify any effect of prolonged exposure to the treatment, the dependent variable will be similarly modelled as a repeated measure on the time of assessment, the treatment arm and their interaction. To maintain interpretability at the patient level, conditional (mixed effects) rather than marginal (GEE) methodology will be used to estimate tolerability trends. Normally distributed random effects will account for the baseline dialysis tolerance in each participant. The treatment and treatment interaction contrasts from the tolerability analyses will be reported as point estimates and 95% confidence intervals.

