#### Tolerability outcome

##### Tolerance to dialysis

Tolerance to dialysis will be assessed by the frequency of intra-dialytic hypotension episodes in the two weeks prior to the assessment time point. Hypotension episodes will be identified according to the NKF-K/DOQI definition (a decrease in systolic BP by ≥20 mMHg or a decrease in mean arterial pressure by ≥10 mMHg associated with one or more of the following symptoms: abdominal discomfort, nausea, vomiting, muscle cramps, restlessness, dizziness, fainting, anxiety and the requirement for fluid boluses) [164]. Measurements will be made at baseline, and the endpoints will consist of measurements at 3, 6, 9 and 12 months. An additional tolerance endpoint will consist in the time-averaged frequency of hypotension episodes over the individual follow-up period.

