Tolerability	ITT	None	Hypotension event counts	Multivariate, mixed effects, allowing for treatment time interaction

Abbreviations: *PP* per protocol, *ITT* intention to treat, *LVMI* left ventricular mass index, *FDR* False Discovery Rate.

All tests of significance of hypotheses concerning treatment effect parameters will be carried out using a level of significance of 5% and two-sided alternatives. The significance threshold of potential covariates will be set at 10%, to promote unbiased and conservative inference. All estimates will be produced as point estimates and as 95% confidence intervals. Unless otherwise noted, model selection when required will be performed using backward selection from the largest model dictated by the situation. Per comparison error rate (PCER) control will be used in all analyses, with the exception of some subgroup analyses where False Discovery Rate (FDR) control will be implemented.

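### As its terms are listed, the tolerability model does not deliver the adjustment for baseline tolerance that its random effects are said to provide

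*Protocol article*

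**What the plan says.** The Tolerance to dialysis section defines the outcome as the "frequency of intra-dialytic hypotension episodes in the two weeks prior to the assessment time point". On timing it says "Measurements will be made at baseline, and the endpoints will consist of measurements at 3, 6, 9 and 12 months", and it adds a time-averaged frequency as a further endpoint.

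The Tolerability analysis section describes two models. The first compares arms "using negative binomial regression of the number of events as dependent variable and the logarithm of the duration of the period covered". In the second, "the dependent variable will be similarly modelled as a repeated measure on the time of assessment, the treatment arm and their interaction". Conditional (mixed-effects) methods are chosen for the trends, and then: "Normally distributed random effects will account for the baseline dialysis tolerance in each participant". The treatment and the interaction contrasts are both to be reported. Table 2 gives the framework as "Multivariate, mixed effects, allowing for treatment time interaction". Neither place names the baseline count as a model term, or says whether the baseline visit is one of the repeated measures.

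Elsewhere baseline is handled explicitly. The primary outcome is analysed by ANCOVA on its baseline value. The Secondary outcomes analysis section has "adjusting for baseline and potentially for other confounding covariates", so baseline is a commitment there and the other covariates are optional.

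**The concern.** A reader of the quoted sentence would conclude that baseline tolerance has been dealt with. A random intercept fitted to post-randomisation counts describes the between-person variation left around each arm's mean. The model assumes it independent of arm, and the baseline count does not inform it. If one arm happens to start with more hypotension-prone participants, part of that difference appears as a treatment effect.

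Putting the baseline visit among the repeated outcomes does not settle the matter by itself. With time, arm and interaction as listed, the arms may differ at baseline. If baseline is the reference time, the treatment term is then the baseline difference, and only the interaction carries the effect. Yet both are to be reported as treatment results.

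The outcome matters. The Study aim and hypothesis section expects tolerance to be no worse on low dialysate sodium, and such a claim rests on interval width. The Background gives hypotension as the most plausible reason for the higher mortality seen with lower dialysate sodium in observational data.

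**Working it through.** **Inputs from the protocol.** One baseline and four follow-up counts over two-week windows (Tolerance to dialysis), and the listed model terms (Tolerability analysis). The only sample-size figure is for LVMI (Power calculation): means 110 and 95 g/m², SDs 40 and 35, correlation 0.75, power 0.80, two-sided alpha 0.05, 25% drop-out, 59 per arm.

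**Reproducing 59.** Residual variance = ((40² + 35²)/2) × (1 − 0.75²) = 1412.5 × 0.4375 = 618, so SD = 24.9. A two-sample comparison of a difference of 15 needs 44 per arm, and 44/0.75 = 58.7, rounded up to 59. The figure reproduces. It does not bear on tolerability except to supply 44 completers per arm.

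**Models compared.** Negative binomial counts Y, random intercept u ~ N(0, τ²), visits 0 (baseline) to 4:

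- (a) follow-up only: log mean = α + β·arm + u
- (b) as (a), plus γ·log(Y₀ + 0.5)
- (c) baseline in the response, common baseline mean: α + δ·post + β·post·arm + u
- (d) as (c), plus θ·arm, so arms are free at baseline; β is the arm-by-post contrast

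The models were fitted by maximum likelihood to 300 simulated trials per setting, with no true effect and complete data. They estimate the average post-baseline contrast, without separate visit effects.

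**Assumed, not in the protocol.** Mean episodes per two weeks 0.3 to 1; SD of the person effect on the log scale 0.5 to 1.5; negative binomial shape 1 to 2; the same person effect at baseline and follow-up. The last assumption favours the baseline term. If tolerance drifts over the year, the gain is smaller.

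**Variance of the log rate ratio, relative to (a):**

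| Mean, SD, shape | SD of estimate, (a) → (b) | (b) | (c) | (d) |
|---|---|---|---|---|
| 0.5, 1.0, 2 | 0.266 → 0.229 | 0.74 | 0.73 | 1.63 |
| 1, 1.0, 2 | 0.246 → 0.212 | 0.74 | 0.72 | 1.35 |
| 1, 0.5, 2 | 0.169 → 0.165 | 0.95 | 0.94 | 2.82 |
| 1, 1.5, 2 | 0.370 → 0.227 | 0.37 | 0.38 | 0.55 |
| 0.3, 0.7, 1 | 0.258 → 0.258 | 1.00 | 1.00 | 3.90 |

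The covariate therefore saves between 1 − 1.00 = 0% and 1 − 0.37 = 63% of the variance. In the second row, the 95% interval for the rate ratio narrows from a factor of exp(1.96 × 0.246) = 1.62 either side to exp(1.96 × 0.212) = 1.52.

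**Chance imbalance.** The estimate was regressed on the between-arm difference in mean log(Y₀ + 0.5):

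| Mean, SD, shape | Slope (a) | (b) | (c) | (d) | SD of baseline difference | Rate-ratio shift at 1 SD, (a) | (b) |
|---|---|---|---|---|---|---|---|
| 0.5, 1.0, 2 | 0.80 | 0.05 | 0.07 | −1.42 | 0.163 | 1.14 | 1.01 |
| 1, 1.0, 2 | 0.64 | −0.03 | −0.03 | −0.95 | 0.197 | 1.13 | 0.99 |
| 1, 0.5, 2 | 0.27 | 0.06 | 0.07 | −1.23 | 0.174 | 1.05 | 1.01 |
| 1, 1.5, 2 | 0.91 | −0.06 | −0.04 | −0.64 | 0.254 | 1.26 | 0.98 |
| 0.3, 0.7, 1 | 0.28 | −0.11 | −0.07 | −3.20 | 0.133 | 1.04 | 0.99 |

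The shift is exp(slope × SD of the difference); for the fourth row, exp(0.91 × 0.254) = 1.26. Model (a) carries the imbalance into the contrast, (b) and (c) remove it, and (d) over-corrects.

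**Average bias.** Mean log rate ratios lay between −0.04 and 0.04 in every model.

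**The case against.** The best defence is that the Tolerability analysis section does not exclude a model in which the quoted sentence is true. If the baseline count is one of the repeated measures and the arms share a baseline mean, the random intercept does adjust; model (c) matched the covariate model. A reader might infer that a random intercept can never account for baseline, and that would be wrong. But the section states no such constraint. It lists a free treatment term, and the endpoint definition points to follow-up counts only.

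Baseline tolerance might also mean only each participant's underlying level. The sentence then describes a random intercept fairly, but the measured baseline count is still unused.

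The Statistical analysis section admits predictors and chance-imbalanced variables as potential covariates at the 10% level, with backward selection. Baseline hypotension could enter that way. That is a possible route, not a commitment, and the primary and other secondary outcomes do not leave their baseline values to it.

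An article may leave the exact form of a baseline term to the analysis plan. This stands for a detail such as log(count + 0.5). It does not cover a stated term list that fails to do what the text says of it.

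The size is also open. Home patients were chosen partly because they are less prone to hypotension, so the gain may lie at the low end. This stands.

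**Conclusion.** The point holds for the model as its terms are listed. With follow-up counts only, the stated accounting for baseline tolerance does not happen. With baseline as a free repeated outcome, the treatment term takes in the baseline difference. The overall comparison has no stated baseline handling.

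Without adjustment, a 1-SD chance imbalance moves the rate ratio by a factor of 1.04 to 1.26, and 0% to 63% of the variance could have been saved. Both ranges rest on the assumed rates, spread and full persistence of the person effect.

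Three stronger conclusions are tempting but not supported:

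- **Bias.** A reader might infer a biased treatment effect. Randomisation balances baseline on average, and the simulated means were near zero. The issue is conditional imbalance and precision.
- **A sure and large loss.** The protocol gives no hypotension rate or spread. One plausible setting showed no gain and another only 5%.
- **The trial's principal harm comparison.** The protocol calls this a tolerability outcome and does not rank it so.

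It is a worthwhile, nearly free correction to a secondary analysis, to be made before unblinding.

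**What to change.** In both tolerability models, take the post-baseline counts as outcomes and add a prespecified fixed baseline term such as log(baseline count + 0.5). Equivalently, put the baseline count in the response with a mean constrained to be common to both arms, and take the treatment effect from the post-baseline contrasts only. State which is used. Keep the random intercept for within-person correlation, and reword the quoted sentence so that it claims no more than that.

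The cost is one extra parameter and a sentence or two of text. The count is already collected before randomisation, and in no simulated setting did the covariate raise the variance (highest ratio 1.00). Adding the randomisation strata is optional and dearer: six centres and two dialysis-hours categories need 5 + 1 = 6 further parameters, with about 44 completers per arm.

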## Discussion

The SoLID trial will be the first randomised controlled trial to investigate the effect lower dialysate [Na+] upon LV structure and function. The outcomes of this research will provide compelling evidence about the efficacy of lower dialysate [Na+] to improve CV outcomes in hemodialysis populations. As importantly, the SoLID trial will provide novel data with respect to important patient centred outcomes, and evaluate the effect of lower dialysate [Na+] on thirst, xerostomia, HRQoL and intra-dialytic hypotension. If the benefit of lower dialysate [Na+] is confirmed, other benefits might also flow on from reduced CV morbidity and mortality, including improvements in general health status, and conceivably fewer hospitalisations and improvements in social/employment rehabilitation. Logistically, lower dialysate [Na+] is a simple and cost-free intervention, and widespread implementation would be easy for home HD patients and selected facility HD patients.

The comprehensive range of secondary outcomes and the use of gold standard measurements further strengthen the trial. These data allows for their simultaneous evaluation as intermediary variables on the causall pathway to LV hypertrophy. Such data have not been previously reported in the setting of clinical trial, where fundamental changes are made to conditions with simultaneous measurement of downstream physiological parameters. Such data will improve understanding of the patho-biology and causall mechanisms of LV hypertrophy, and in particular the contributions of uncontrolled hypertension and ECF overload. Data from the SoLID trial will allow the development of a hierarchy of importance for the various factors that increase LV mass. There is a strong likelihood of novel relationships and hypotheses emerging, in turn leading to further research in both bench and clinical settings.

In terms of internal validity, the strengths of the SoLID trial are that it is prospective and randomised, with robust allocation concealment and analysis of cardiac MRI data in duplicate by two blinded independent analysts who will remain unaware of the allocation of participants for the duration of the trial. A limitation of the trial pertains to secondary outcomes. All baseline measurements of secondary outcomes will be made prior to randomisation. However, once randomisation has occurred, participants and assessors for the follow-up measurements will not be blinded to treatment. For instance, bioimpedance and pulse wave procedures and measurements will be performed by research associates who will be potentially aware of the allocation of participants. This may bias participants’ and research associates’ perception of tolerance to the intervention, and their reporting of subjective scoring surveys such as thirst and xerostomia inventories and HRQoL questionnaires. The impact of any actual bias is likely to be mitigated through completion is baseline measurements prior to randomisation, but certainly not abrogated.

Of note, the SoLID Trial excludes those who are on dialysis more than 3.5 times per week to avoid confounding the effect of dialysate [Na+] on LV mass by frequent or nocturnal dialysis. The study will not exclude those whose HD treatments are unconventionally long (~8 hours per treatment) so long as they are undergoing HD no more than 3.5 times per week. This is based on the high reported prevalence of LV hypertrophy in populations treated with this manner (notwithstanding the overestimation of LV mass by echocardiography that biases these studies [175]): 87% of patients in Christchurch NZ [124], 76% of those in Manchester UK [177], and in more than 80% of those in Tassin France [178]. LV hypertrophy is still present in these populations on long-hour dialysis as a result of BP variability, neurohormonal factors and residual positive sodium balance, all of which are potentially modifiable with lower dialysate [Na+].

In terms of external validity, the major limitation of the SoLID trial is the research setting of home HD. Participants are likely to have less medical co-morbidity than facility HD patients, a factor that was a prime consideration in the development of the sampling frame for the SoLID trial. Such patients are less prone to intra-dialytic hypotension, which minimizes the chances of participant dropout from intolerance to the lower dialysate [Na+] in the trial. As a result, the SoLID trial may not be immediately applicable to dialysis patients with a high burden on medical co-morbidity who are more prone to intra-dialytic hypotension. Notwithstanding, the SoLID trial may provide valuable proof-of-concept data for future research in this patient population, depending on the clinical characteristics of patients eventually recruited to the trial.

As with any clinical trial, recruitment will be a key element. Feasibility analysis of the participating 6 centres has indicated a sufficiently large pool of potential participants assuming a 33% conversion rate. A pilot study previously undertaken by the SoLID research group showed good tolerance to lower dialysate with minimal adverse events, and we do not anticipate excess loss of participants due to intolerance of the trial intervention [89]. The 25% dropout rate we modelled in power calculations accounts for technique failure in the modern NZ home HD population. A potential risk to recruitment lies with the collection of so many secondary endpoints and their need to occur at specific times on the participants’ dialysis schedules, which may make the trial unattractive to some patients. Slow recruitment will be managed by the expansion of the SoLID trial to include a 7^th^ site in NZ or Australia, as required.

In conclusion, the SoLID trial will provide compelling evidence about the use of lower dialysate [Na+] to improve CV outcomes, and potentially improve understanding of the biological mechanisms underlying the development and persistence of LV hypertrophy. If the benefit of lower dialysate [Na+] is confirmed, the SoLID Trial will contribute a cost-free economically sustainable improvement to dialysis practice. This, and the immediately availability of the intervention to HD patients, will allow for optimal and maximal translation into clinical effectiveness and benefit.

## Abbreviations

HD: Hemodialysis; ESKD: End-stage kidney disease; ANZDATA: Australian and New Zealand dialysis and transplant registry; SCD: Sudden cardiac death; LV: Left ventricular; LVH: Left ventricular hypertrophy; ECF: Extra-cellular fluid; BP: Blood pressure; IDWG: Intra-dialytic weight gain; LVMI: Left ventricular mass index; CAMRI: Centre for advanced magnetic resonance imaging; DMC: Data monitoring committee; CV: Cardiovascular; CKD: Chronic kidney disease; LDL: Low density lipoprotein; IVRS: Interactive voice response system; NHMRC: National (Australia) health medical research Council; CTC: MRI: Magnetic resonance imaging; NT-pro-BNP: N Terminal pro Brain Natretic Peptide; BCM: Body composition monitor; hsCRP: high sensitivity C-Reactive Protein; PWV: Pulse wave velocity; PWA: Pulse wave analysis; SD: Standard deviation; PTT: Pulse transit time; ϒNa: Ionic sodium; NKF-K/DOQI: National kidney foundation kidney disease outcomes quality initiative; HRQoL: Health related quality of life; SOLID: Sodium lowering in dialysis; ANCOVA: Analysis of Co-variance; ITT: Intention to treat; PP: Per protocol; PCER: Per comparison error rate; GEE: Generalised estimating equation; FDR: False discovery rate.
